## Introduction

Community treatment orders (CTOs), a form of supervised community treatment (SCT), were introduced to the Mental Health Act (2007) (MHA) in England and Wales in 2008 and allow certain patients detained in hospital to continue treatment in the community following discharge under specific conditions. To be eligible for a CTO, a patient must be detained in hospital under the MHA on a section that allows for compulsory treatment. The most common inpatient treatment orders are sections 3 and 37, the former being a civil order and the latter a forensic, court-imposed equivalent for mentally ill offenders. A CTO provides the clinical team the power to recall the patient to hospital after discharge.

At CTO initiation (the point of discharge from inpatient care), there are two mandatory conditions, namely that the person subject to a CTO makes themselves available for assessment for its renewal and (where necessary) to be seen by an approved second opinion doctor (SOAD) for the purposes of assessing proposed treatment plan should the patient lack capacity in respect of their treatment. Discretionary conditions can also be specified which most often include treatment (ie, medication) adherence and engagement with services (eg, attending for appointments with professionals). CTOs do not permit compulsory (ie, forcible) treatment in the community,^1^ but those who default from these conditions may be recalled to hospital for assessment if there are grounds to suspect deterioration in their mental health and/or risk to the patient or others. Where this assessment indicates the need for further treatment, the CTO is revoked and the original treatment order applies.

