## Methods and analysis

### Data sources and study outcomes

The use of CTOs in England is recorded as part of a mandatory administrative dataset, the MHSDS, formerly known as the Mental Health Minimum Dataset, and then the Mental Health and Learning Disabilities Dataset.^23^ MHSDS collates monthly returns from health service providers on all patients in contact with secondary mental health services provided and/or funded by NHS England. This includes voluntary and involuntary inpatient treatment, outpatient attendance, day treatment and other episodes of secondary mental healthcare.

MHSDS data are based on spells of care for individual patients. Since 2011, the dates on which specific care spells start and end have been included. Care spell dates can therefore be used to determine duration of CTO use and hospital (re)admissions. Four years of MHSDS data will be used covering the period 2011/2012 to 2014/2015, hereafter referred to as the study period. MHSDS records contain a unique patient identifier code which will be used to link patient care spells across the study period. This identifier will also be used to link patient records to the Office for National Statistics (ONS) Mortality Database, to ascertain patient deaths. Access to and linkage of, these different administrative data sets will be facilitated by the ESRC Administrative Data Research Network.

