Next, to examine associations between CTO use and a range of outcomes, a cohort of patients will be constructed consisting of a treatment group (those who have been on a CTO) and a matched control group (those who are eligible but who have not been on a CTO). To prevent bias arising from secular changes in clinical practice, we will frequency match these groups according to the start date of the CTO (CTO group) and the end date of the CTO-eligible section of the MHA (non-CTO group), with tolerance limits determined after inspection of the data. As these dates are the point within the study period at which patients in both treatment groups are discharged from hospital, they represent the index date for each arm of the study. Models based on the cohort of matched patients will be used to test associations between SCT use and patient outcomes: total time spent in hospital, time to first readmission and mortality. For total time spent in hospital, count models based on Poisson or negative binomial distributions will be estimated. For time to first readmission, discrete-time survival analysis models will be estimated. For mortality, binary response models based on the logistic distribution will be estimated. To control for confounding by indication, we will adjust analyses for the propensity of being placed on SCT,^33^ with propensity scores being modelled using the pool of available variables which will include age, sex, ethnicity, diagnosis and previous admissions (where known). CCMMs based on this cohort will be used to test for the overall ‘average’ effect of CTO on each of the study outcomes. The models will also assess whether there is significant spatial and temporal variation around these average effects and estimate the extent to which this is associated with patient, local area and health service characteristics, including the length of time that patients are on CTOs.

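### Controls are indexed at the end of an MHA section, which the plan equates with hospital discharge without support; where the section ends first, follow-up starts in hospital for controls only

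*Protocol article*

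**What the plan says.** The Data analysis section of the protocol article builds a cohort of CTO patients and eligible patients who have not been on a CTO. It frequency matches them on "the start date of the CTO (CTO group" and on "the end date of the CTO-eligible section of the MHA (non-CTO group". These two dates also serve as the index dates, and the reason given is: "As these dates are the point within the study period at which patients in both treatment groups are discharged from hospital".

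Three outcomes are then modelled on this cohort: "total time spent in hospital, time to first readmission and mortality". The Abstract names total time in hospital as primary.

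Three other statements bear on the point:

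- The Introduction describes the CTO date as a discharge date: "At CTO initiation (the point of discharge from inpatient care".
- The Introduction limits eligibility to some kinds of detention: "a patient must be detained in hospital under the MHA on a section that allows for compulsory treatment".
- Data sources and study outcomes says of the dataset's coverage: "This includes voluntary and involuntary inpatient treatment". It also says that dates of admission can be recovered: "Care spell dates can therefore be used to determine duration of CTO use and hospital (re)admissions".

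**The concern.** The two index dates are different kinds of event. CTO start is described as the moment of leaving inpatient care. The end of a section is the end of a legal status. If that status can end while the patient is still on the ward, the two arms start their follow-up clocks at different points in care.

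All three outcomes depend on that clock. Residual days of the index admission would add to control bed days but could not add to CTO bed days. A control still in hospital cannot be readmitted, so the survival model would contain event-free time that is not time at risk. A death between section end and discharge would count after the index date in a control, whereas a CTO patient has to reach discharge to be indexed at all.

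Adjustment for the propensity score does not help. It balances who receives a CTO, not when counting begins. The problem would also pass into the economic stage, which takes its inputs from these models and compares bed days.

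**Working it through.** **1. Is the equation with discharge supported in each arm?**

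| | CTO group | Control group |
|---|---|---|
| Index date | CTO start | End of eligible section |
| Called discharge in Data analysis | Yes | Yes |
| Tied to discharge elsewhere | Yes, Introduction | No |
| Rule if the date and discharge differ | None stated | None stated |
| Restricted to patients discharged that day | Not needed if the Introduction holds | Not stated |

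The dataset includes voluntary inpatient care, so being an inpatient is not the same as being on a section. Eligibility covers only sections that allow compulsory treatment, so the end of an eligible section need not be the end of all detention. Both statements leave room for a control to be in hospital after the index date. Neither says that this happens, or how often.

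**2. Primary outcome.** The article gives no sample size, event count or expected bed days, so there is no planned figure to reproduce. The following is an illustration on assumed inputs, with no true CTO effect:

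- m = mean post-discharge hospital days, the same in both arms (assumed 60)
- p = share of controls who stay on after section end (assumed 10% to 50%)
- L = mean extra days among them (assumed 14 to 42)

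Control mean = m + p × L. Spurious relative reduction for CTOs = pL / (m + pL).

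| p | L | pL | Reduction |
|---|---|---|---|
| 0.10 | 14 | 1.4 | 1.4 / 61.4 = 2.3% |
| 0.30 | 28 | 8.4 | 8.4 / 68.4 = 12.3% |
| 0.50 | 42 | 21 | 21 / 81 = 25.9% |

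A second grid varies m as well (p 10% to 50%, L 7 to 28 days, m 30 to 120 days). The CTO-to-control ratio of means under no effect runs from 120 / 120.7 = 0.994 to 30 / 44 = 0.682. The formula adds the extra stay to the post-discharge days. With a fixed end of follow-up, the extra stay would displace some post-discharge time and the excess would be somewhat smaller.

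**3. Time to first readmission.** Each extra day is event-free by construction. Control readmissions are pushed later on the clock, so the distortion favours controls, the opposite direction to step 2.

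**4. Mortality.** Let r be the post-discharge risk in both arms (assumed 2% to 5%) and q the control risk of dying between section end and discharge (assumed 0.1% to 1%). Control risk = 1 − (1 − q)(1 − r).

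- r = 5%, q = 0.1%: control risk 5.095%; odds ratio (0.05 / 0.95) / (0.05095 / 0.94905) = 0.98.
- r = 2%, q = 1%: control risk 2.98%; odds ratio (0.02 / 0.98) / (0.0298 / 0.9702) = 0.66.

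This shows direction only. The document does not say how such deaths are handled.

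**5. After the fix.** With both arms indexed at live discharge, pL = 0 and q = 0, and both ratios return to 1.00.

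**The case against.** The strongest reply is that the plan already says what it intends: both dates are discharge dates. If that is taken at its word, there are no residual days. Accepting the parenthetical about CTO start while doubting the matching statement about section end may look uneven. The link between section records and spell records is also the kind of detail that a journal article leaves to a fuller document. And if controls do stay longer because no CTO was used, those days may be part of the effect of interest, since least restrictive treatment was one motive for CTOs.

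Parts of this stand. The document does not report continued stay, gives no frequency, and does not spell out that days and deaths are counted from the index date, although that is the natural reading. A reader might infer that voluntary days and in-hospital deaths are in fact being charged to controls; the text supports only that they would be, wherever section end comes first. A reader might also infer that a section ended by death yields a control death on day 0. The text can equally be read as excluding such patients, because they were not discharged.

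The rest does not remove the point. This is a stated rule with a stated premise, not an omitted detail, and followed as written it selects a legal date. The uneven treatment is justified because only CTO start has support elsewhere, and the article's own description of the dataset separates inpatient care from detention. As to the effect of interest, the plan's declared aim is to start at discharge in both arms, and indexing at actual discharge carries that out.

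**Conclusion.** The concern holds in conditional form. The control index date is a legal date equated with discharge without independent support. Followed literally, the rule can start follow-up in controls who are still inpatients. Three consequences follow, with decreasing certainty:

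- Primary outcome: bias in favour of CTOs.
- Time to first readmission: bias in favour of controls.
- Mortality: possible bias in favour of CTOs, on a weaker inference.

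This rests on two conditions: that some eligible sections end before discharge, and that outcomes are counted from the index date.

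The size cannot be derived from the document. On the assumed inputs, the spurious reduction in bed days is about 2% to 26%. The mid-range 12% should not be read as an estimate, because every input to it is assumed. The wider grid reaches down to a bias of 0.6% (ratio 0.994), so a negligible effect is not excluded. The case for acting is that the asymmetry touches the primary outcome, propensity adjustment cannot remove it, and correction is cheap before the data are analysed.

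**What to change.** Define the index date in both arms as the actual date of discharge, alive, from the inpatient spell that contains the eligible section (controls) or the CTO start (CTO group). Take it from the care-spell dates. Frequency match on that date. State that hospital days, readmission and death are all counted from it. A control whose eligible section ends while the admission continues is then indexed at the end of that admission.

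The cost is one definition and a link between section and spell records. Spells with no recorded discharge date need a rule, or they drop out. Any extra index-stay days in controls also leave the primary outcome. Because these could partly reflect not using a CTO, report a sensitivity analysis indexed at section end, together with the share of controls whose section end and discharge differ and by how many days. That would also supply the figures the document lacks.

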**Figure 1 F1:**
[figure not shown]
An illustration of cross-classified multilevel data.

Analysis will be conducted in three stages. First, CCMMs based on all patients eligible for CTOs will be used to explore spatial and temporal variation in the use of CTOs. CTO use will be considered as a binary outcome (patients subject to a CTO during the study period vs those who were not) and analyses will be undertaken using logistic multilevel regression. Models will estimate the variation at each level in the risk of being on a CTO and assess the extent to which any variation in this outcome is associated with patient, local area and health service characteristics. We will also investigate the duration of time spent subject to CTO (in days). Poisson/negative binomial link function CCMMs will be used and will include offset variables to take account of different observation times for patients.^32^

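### Mortality is fixed as a yes/no logistic outcome although length of follow-up depends on index date, so mortality differences by index year would mainly reflect observation time

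*Protocol article*

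**What the plan says.** All references are to the protocol article.

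- **Mortality model** (Data analysis): "For mortality, binary response models based on the logistic distribution will be estimated". No window, minimum follow-up, exposure term or end date for deaths accompanies it.
- **Study period** (Data sources and study outcomes): "Four years of MHSDS data will be used covering the period 2011/2012 to 2014/2015". Deaths come from linkage to the ONS Mortality Database; the end date of that linkage is not given.
- **Start of follow-up** (Data analysis): the index date is "the point within the study period at which patients in both treatment groups are discharged from hospital".
- **Matching** (Data analysis): the two groups are frequency matched on calendar index date to guard against secular change, "with tolerance limits determined after inspection of the data".
- **Time in the other analyses** (Data analysis): the models for days on a CTO "will include offset variables to take account of different observation times for patients". For readmission: "For time to first readmission, discrete-time survival analysis models will be estimated".
- **Target**: the outcome models are to test the average CTO effect and assess "whether there is significant spatial and temporal variation around these average effects". The opening of Data analysis is broader and gives variation in CTO use and in outcome as the overarching aim.

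**The concern.** A logistic model for died/not died treats a patient observed alive for a few months and one observed alive for more than three years as the same non-event. Because index dates fall throughout the period that also supplies follow-up, early-index patients have had much longer in which to die. Any comparison of mortality across index years then mixes the death rate with the length of observation.

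This matters because temporal and spatial variation in outcomes is the declared subject of the study, and the article says its modelling approach will give unbiased measures of that variation. A falling mortality gradient by index year could be read as a change in practice or safety when it is administrative. The plan recognises unequal observation time in two other analyses and chooses a form for mortality that, as stated, does not carry it.

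**Working it through.** The article gives no mortality rate, event count or sample size, so there is no stated figure to reproduce. What follows sizes the effect under declared assumptions.

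**Inputs.** From the article: a four-year period, index dates within it, and a logistic model. Assumed: constant death rate h of 1%, 2% or 3% per year, index dates uniform over the period, deaths counted to the end of 2014/2015.

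**1. Mortality by index year.** Patients indexed mid-year in years 1 to 4 have t = 3.5, 2.5, 1.5 and 0.5 years of follow-up. Risk is 1 - exp(-ht), so the odds are exp(ht) - 1.

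- At h = 0.02 the risks are 6.8%, 4.9%, 3.0% and 1.0%.
- Odds ratio, year 1 versus year 4, = [exp(3.5h) - 1] / [exp(0.5h) - 1]:
  - h = 0.01: 0.03562 / 0.00501 = 7.1
  - h = 0.02: 0.07251 / 0.01005 = 7.2
  - h = 0.03: 0.11071 / 0.01511 = 7.3

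The true death rate is the same in every year, so the whole ratio is artefact.

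**2. Later end of linkage.** If deaths were counted for one further year (assumed), t becomes 4.5 and 1.5. At h = 0.02 the ratio is [exp(0.09) - 1] / [exp(0.03) - 1] = 0.09417 / 0.03046 = 3.1. The artefact shrinks but does not vanish.

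**3. Average CTO effect, arms matched on index date.** Average the risk over t uniform on 0 to 4 years in each arm.

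- No true effect: odds ratio 1.00.
- Assumed true hazard ratio 0.8: odds ratio 0.799 at h = 0.01 and 0.798 at h = 0.02.

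**4. Drift of the CTO effect by index year.** Odds ratio = [exp(0.8ht) - 1] / [exp(ht) - 1]. At h = 0.02 it is 0.05760 / 0.07251 = 0.794 for t = 3.5, and 0.00803 / 0.01005 = 0.799 for t = 0.5. Even at 5% per year it moves only from 0.786 to 0.798.

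**5. Imperfect matching.** Shift one arm's index dates later by d years, with follow-up floored at zero and no true effect. At h = 0.02:

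- d = 0.1: odds ratio 1.05
- d = 0.25: mean follow-up 2.00 versus 1.76 years; mean risks 3.90% and 3.43%; odds ratio 0.04053 / 0.03551 = 1.14
- d = 0.5: odds ratio 1.31

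**6. Areas and providers.** With mean follow-up of 2 years and uncommon deaths, a between-provider SD of s years in mean follow-up adds an SD of about s/2 on the log-odds scale. Against an assumed true provider SD of 0.2, the artefactual share of variance is (s/2)² / [(s/2)² + 0.04]:

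- s = 0.1: 0.0025 / 0.0425 = 6%
- s = 0.2: 0.01 / 0.05 = 20%
- s = 0.4: 0.04 / 0.08 = 50%

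Chance alone gives s = (4/√12)/√n, which is 0.16, 0.08 or 0.05 years for n = 50, 200 or 500 patients per provider. Larger values need systematic differences in index dates, on which the article has no data.

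**The case against.** The strongest reply has four parts.

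**The odds ratio of 7 concerns raw mortality.** The outcome models are aimed at the CTO effect and the variation around it, and steps 3 and 4 show that both barely move when arms share the same index dates. This stands. A reader might infer that the CTO effect on mortality, or its trend over time, will be spurious; the plan does not support that, because matching roughly balances potential follow-up. Two things remain. The stated aim also covers variation in outcome itself, and the protection depends on a matching tolerance not yet fixed.

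**The spatial effect is not demonstrated.** This also stands. A reader might infer that variation between areas and providers will largely reflect length of observation. That would need index-date distributions to differ materially between them, and nothing in the article says they do.

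**The spread of follow-up is inferred.** Follow-up running from nearly four years down to zero assumes that deaths are counted only to the end of 2014/2015. A later end date reduces the relative spread, as step 2 shows, but does not equalise follow-up.

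**A condensed article may leave a window or time covariate to a fuller plan.** Fair, and silence about such details is not the point. The point is that the article does state a model form for mortality, and that form, unlike those for readmission and days on a CTO, does not carry observation time.

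**Conclusion.** The point holds in a limited form. The plan fixes a binary logistic model for an outcome whose observation time varies with index date, and states nothing that equalises or adjusts for that time. Under a constant 1-3% annual death rate, uniform index dates and deaths counted to the end of 2014/2015, mortality differs between first- and last-year cohorts by an odds ratio of about 7 with no true change. With later linkage it is less.

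Distortion between areas or providers is possible but unquantified. The average CTO effect is largely protected by matching if the tolerance is tight; an assumed 0.25-year shift would create an odds ratio of about 1.14. As mortality is a secondary outcome and its main comparison is roughly protected, this should be fixed but does not undermine the study.

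**What to change.** Either of two changes would do.

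1. Model time from index date to death with a discrete-time survival model in the same cross-classified framework, censored at a stated end of ONS linkage. This model type is already planned for readmission. It needs the linkage to supply the timing of deaths; the article says only that deaths will be ascertained. The link function, which the article does not name, should be stated.
2. Keep a binary outcome, but define it as death within a fixed window from the index date, among patients with at least that much potential follow-up.

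Under a constant hazard, either change brings the artefactual year 1 versus year 4 odds ratio to 1.0. In both cases, state the end date for counting deaths and report the distribution of index dates by arm after matching, so that the tolerance can be judged.

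Cost: the survival model needs a larger person-period dataset and longer MCMC runs. The fixed window excludes some late-index patients and ignores deaths after the window.

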**Methods and analysis:**

Four years of data from the Mental Health Services Dataset (MHSDS) will be analysed using multilevel models. Models based on all patients eligible for CTOs will be used to explore variation in their use. A subset of CTO-eligible patients comprising a treatment group (CTO patients) and a matched control group (non-CTO patients) will be used to examine variation in the association between CTO use and study outcomes. Primary outcome will be total time in hospital. Secondary outcomes will include time to first readmission and mortality. Outputs from these models will be used to populate predictive models of healthcare resource use.

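### The primary outcome is hospital days, yet prior hospital days are not named in the confounding adjustment; adding them would be a cheap improvement

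*Protocol article*

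**What the plan says.** The abstract of the protocol article states: "Primary outcome will be total time in hospital". The Data analysis section sets out how the second stage handles it:

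- Model: "For total time spent in hospital, count models based on Poisson or negative binomial distributions will be estimated".
- Matching: "we will frequency match these groups according to the start date of the CTO (CTO group"), with the end date of the eligible section used for controls. Calendar date is the only matching factor.
- Confounding: "To control for confounding by indication, we will adjust analyses for the propensity of being placed on SCT".
- Content of the score: the article describes "propensity scores being modelled using the pool of available variables which will include age, sex, ethnicity, diagnosis and previous admissions (where known").
- Other terms: the models also assess variation around the average effect. They will "estimate the extent to which this is associated with patient, local area and health service characteristics, including the length of time that patients are on" a CTO.

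On the data, the section on data sources says that spell start and end dates have been included since 2011: "Care spell dates can therefore be used to determine duration of CTO use and hospital (re)admissions". The window is fixed: "Four years of MHSDS data will be used covering the period 2011/2012 to 2014/2015, hereafter referred to as the study period".

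**The concern.** The outcome is measured in days, but the one history variable named for adjustment is previous admissions. If that is coded as a count, one earlier admission of 20 days and one of 200 days look the same. A propensity score also orders patients by their chance of a CTO and not by expected bed use, so patients with equal scores can differ widely in past hospital days.

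The Introduction gives reduction of revolving-door admissions as a reason for introducing CTOs, so earlier hospital use is part of the indication. That statement is about admissions. Whether length of stay also drives selection is an assumption. If it does, a measurable confounder stays partly uncontrolled in the primary comparison. If it does not, leaving it out costs only precision.

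The estimate also feeds the third-stage cost projections. Their probabilistic sensitivity analysis draws on parameter uncertainty from the fitted models, which does not include confounding bias.

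**Working it through.** The article states no sample size, effect size, variance or correlation, so there is no figure to reproduce. What follows illustrates size on assumed inputs.

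**Set-up.** Let L be standardised log prior hospital days and A a standardised admission measure with correlation r to L.

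- CTO selection: logit P(CTO) = log(0.3/0.7) + gL. The 30% comes from the Introduction.
- Later hospital days: log mean = 4 + bL, negative binomial with dispersion 1.5, true CTO rate ratio 1.0.
- Assumed ranges: r = 0.4 to 0.8, g = 0 to 0.6, b = 0.3 to 0.6. There were 20,000 patients per data set and 6 data sets per cell.

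**Selection depends on prior days.** Each cell shows the rate ratio with a score on A only, then with prior days added to the outcome model.

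| r | g=0.3, b=0.3 | g=0.3, b=0.6 | g=0.6, b=0.3 | g=0.6, b=0.6 |
|---|---|---|---|---|
| 0.4 | 1.059; 0.982 | 1.136; 0.986 | 1.157; 1.009 | 1.301; 0.986 |
| 0.6 | 1.069; 1.004 | 1.132; 1.002 | 1.114; 0.996 | 1.248; 0.992 |
| 0.8 | 1.036; 1.005 | 1.059; 0.996 | 1.064; 1.001 | 1.139; 1.001 |

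The range is 1.04 to 1.30 before and 0.98 to 1.01 after. The Monte Carlo error of a cell on the log scale is about 0.02/√6 = 0.008, so most small departures from 1.0 are noise.

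**Hand check.** The residual bias on the log scale is roughly b × g × (1 − r²).

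- r = 0.6, g = b = 0.6: 0.36 × 0.64 = 0.230, and exp(0.230) = 1.26, against 1.248 simulated.
- r = 0.8, g = b = 0.3: 0.09 × 0.36 = 0.032, and exp(0.032) = 1.03, against 1.036 simulated.

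The sign follows g. If patients with longer stays were less likely to receive a CTO, the bias would run the other way.

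**Selection does not depend on prior days (g = 0).** Count-only adjustment gave 0.99 to 1.01, so no material bias. The standard error of the log rate ratio fell from 0.0195–0.0242 to about 0.019. The smallest fall is (0.0195 − 0.0190)/0.0195 = 3%; the largest is (0.0242 − 0.0191)/0.0242 = 21%.

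**A second data model.** This used Poisson admissions with a relapse frailty, lognormal stays with a patient effect, a score from age and admission count, and 25 cohorts of 20,000.

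| Log-odds of CTO per SD of stay length | Score only | Score plus baseline days |
|---|---|---|
| 0 | 0.99 | 0.99 |
| 0.15 | 1.08 | 1.05 |
| 0.30 | 1.18 | 1.12 |

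The share of excess removed is (0.08 − 0.05)/0.08 = 38% and (0.18 − 0.12)/0.18 = 33%.

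**What the two show together.** Adding prior days reduces the bias in both whenever stay length drives selection. How much goes depends on the data model: nearly all in the first, where the recorded variable is the confounder itself, and about a third in the second. In the first, a score built on prior days gives the same results as entering days in the outcome model, because that score is a linear function of days. It therefore cannot rank the two placements.

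**The case against.** The strongest reply is that this is a condensed article. The covariate list is introduced as examples from a wider pool, and the Covariates section describes care clusters and outcome ratings that may also carry severity. The full list may stand in a plan that is not shown. This reply stands, and it rules out several stronger readings that a reader might infer:

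- *Prior days are excluded from adjustment.* The article does not name them, but it does not exclude them. The spell dates make them available to the pool.
- *Prior use enters only as a count.* The article never defines previous admissions. The term could cover number, duration or both.
- *Prior days are the strongest baseline predictor.* Nothing in the documents supports that ranking.
- *Reliance on a propensity score is itself an error.* A well-specified score that contains prior days would control this confounding. Direct entry mainly adds precision and robustness.
- *The outcome models contain nothing but the score.* Patient characteristics also enter, although the article gives their purpose as explaining variation around the average effect.

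It is also fair that every simulation input is assumed, that the simulated scores omit variables the plan names, and that nothing shows precision to be limiting in a national data set. The article acknowledges confounding by indication and residual confounding. That does not replace use of a confounder that can be measured from the data held.

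**Conclusion.** The point holds as an improvement to the stated adjustment, not as a demonstrated error. The article specifies its matching factor, its method of confounding control and its named history variable, and in none of these places does it name the pre-index value of the primary outcome. The benefit is conditional. If stay length influences CTO selection, count-only adjustment could shift a null rate ratio to about 1.04 to 1.30 under the assumed ranges. If it does not, there is no material bias and the gain is modest precision. The documents do not show which case applies, and the range presumes that previous admissions means a count.

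**What to change.** Derive hospital days over a fixed look-back ending at the start of the index admission, for example log(1 + days in the prior 12 months) plus an indicator for none. Include this in the propensity score, and enter it directly beside the score in the outcome models, above all the one for total time in hospital. Define previous admissions at the same time.

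The derivation needs no new data. The real cost is incomplete history. With four years of data and index dates spread evenly (an assumption), 1/4 = 25% of patients are indexed in the first year and lack a full 12-month look-back. The share is somewhat larger in practice, because the look-back ends at admission and the index date is discharge. Either add a term for observed look-back time, or keep all patients in the main analysis and run a sensitivity analysis restricted to those with complete look-back.
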